## Abstract

**Background:**

Hip fracture represents a substantial acute inflammatory trauma, which may constitute a significant insult to the degenerating brain. Research suggests that an injury of this kind can affect memory and thinking in the future but it is unclear whether, and how, inflammatory trauma injures the brain. The impact of Acute SystematiC inflammation upon cerebRospinal fluId and blood BiomarkErs of brain inflammation and injury in Dementia: a study in acute hip fracture patients (ASCRIBED) explores this relationship, to understand the effect of inflammation on the progression of dementia.

**Methods:**

This protocol describes a multi-centre sample collection observational study. The study utilises the unique opportunity provided by hip fracture operations undertaken via spinal anaesthesia to collect cerebrospinal fluid (CSF) and blood, to investigate the impact of acute brain inflammation caused by hip fracture on the exacerbation of dementia. We will recruit 200 hip fracture patients with a diagnosis or evidence of dementia; and 200 hip fracture patients without dementia. We will also recruit ‘Suitable informants’, individuals in regular contact with the patient, to provide further proxy evidence of a patient’s potential cognitive decline. We will compare these 400 samples with existing CSF and blood samples from a cohort of dementia patients who had not experienced a systemic inflammatory response due to injury. This will provide a comparison between patients with and without dementia who are suffering a systemic inflammatory response; with stable patients living with dementia.

**Discussion:**

We will test the hypothesis that hip fracture patients living with dementia show elevated markers of brain inflammation, as well as neuronal injury and Alzheimer-related plaque pathology, in comparison to (1) stable patients living with dementia and (2) hip fracture patients without dementia, as measured by biomarkers in CSF and blood. The findings will address the hypothesis that systemic inflammatory events can exacerbate underlying dementia and inform the search for new treatments targeting inflammation in dementia.

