#### Secondary objectives

To determine whether the magnitude of the brain inflammatory response predicts the quantity of specific brain injury markers measured in the CSF. Magnitude of the brain injury will be assessed via brain injury markers T-tau, P-tau, NfL, neurogranin, synaptotagmin and SNAP-25 in CSF. We will also examine if patients who are Aβ-positive at baseline are more or less likely to have dementia or develop dementia at follow-up. We will also look for interactions of Aβ positivity with the other biomarkers in regards to clinical outcome.

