#### Post-op 48 h (± 4 h)

2 × 5.0 ml blood (serum tube) will be collected from the patient. Every effort will be made to collect post-operative bloods within this time window, but this may not always be possible. Therefore, research nurses will collect the MMSE~ 2: SV data and bloods at the next earliest opportunity but not beyond 60 h post-op. The time point at which these samples and data are collected will be noted and fed into the analysis. Sites consistently collecting samples outside the 48 (± 4 h) window will be reviewed by the Study Management Group (SMG) who will decide if they should be withdrawn. For patients recruited on a Thursday or Friday, it is accepted that this follow-up may not be possible due to insufficient Research Nurses across weekends.

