## Discussion

Despite significant investment, disease-modifying treatments for dementia are still absent and there has been no significant treatment breakthrough for 15–20 years [28]. Inflammation is a vital part of the immune system’s response to injury and infection which may become harmful if exaggerated or unresolved. There is now growing evidence that harmful inflammation in the brain is aetiological and contributed to the pathophysiology of dementia [29].

Recent research highlights acute illnesses or injuries that cause inflammation throughout the body, such as infection, trauma and surgery, can accelerate the speed of decline in dementia [30, 31]. For example, an infection in a hospitalised older person with dementia is linked to a higher long-term worsening of that person’s symptoms. The underlying mechanisms linking inflammation, cognition and dementia progression remain greatly under-researched, with almost no studies in humans. This lack of research impacts on the search for new treatments targeting inflammation in dementia.

Thus this study will develop understandings of the role of inflammatory response in dementia and support developing pharmaceutical interventions. Additionally it will inform ways to predict deterioration in dementia. Exploration of new potential disease pathways remains essential for finding new therapeutic targets.

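### The schedule has no direct cognitive test after 60 h, and the 1-month evidence defines the dementia group, so progression, exacerbation and newly developed dementia cannot be observed

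*Protocol article*

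**What the plan says.** **Aims and conclusions.** The Abstract (Background) gives the purpose as "to understand the effect of inflammation on the progression of dementia". The Abstract (Methods) says the samples will be used "to investigate the impact of acute brain inflammation caused by hip fracture on the exacerbation of dementia". The Abstract (Discussion) adds: "The findings will address the hypothesis that systemic inflammatory events can exacerbate underlying dementia". The main Discussion says: "Additionally it will inform ways to predict deterioration in dementia".

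**Secondary objectives.** Two of these look beyond the biomarkers. One asks whether patients who are Aβ-positive at baseline are "more or less likely to have dementia or develop dementia at follow-up". The other concerns "interactions of Aβ positivity with the other biomarkers in regards to clinical outcome". The article does not define that clinical outcome.

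**Schedule.** Table 1 places the single CSF sample on the day of operation. AMT/4AT appears before surgery and in the 48 h column, and the MMSE-2 in the 48 h column only. The section on the 48 h contact sets the outer limit: "research nurses will collect the MMSE~ 2: SV data and bloods at the next earliest opportunity but not beyond 60 h post-op". It accepts that the visit may be missed for patients recruited on a Thursday or Friday. The 1-month section describes a GP and case-note review for a dementia diagnosis already on file, some further unspecified clinical measures and test results, and the IQCODE if still outstanding. No later contact is listed.

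**The concern.** Progression and newly developed dementia are changes over time, and observing them needs an assessment after the acute period. The Background section itself separates short-term delirium from cognitive decline, and acute from lasting cognitive effects. The consent section notes that capacity lost through delirium may return. The only MMSE-2 falls within that acute period. A biomarker association with it could reflect dementia severity before the fracture, transient delirium or the start of a lasting decline, and one measurement cannot separate these.

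If the objectives stay as worded, the study commits itself to two secondary questions that its data cannot answer, and to conclusions about the course of dementia that no result could support. The direction and strength of the biomarker findings would not alter this.

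**Working it through.** **1. The plan's own figure.** The Sample size section states 90% power for 0.33 SD with 200 per group, two-sided 5%.
- Detectable difference: (1.960 + 1.282) × √(2/200) = 3.242 × 0.1 = 0.324 SD.
- Power at 0.33 SD: Φ(0.33/0.1 − 1.960) = Φ(1.34) = 0.91.
- With R² of 0.25: 0.324/√(1 − 0.25) = 0.374, stated as around 0.37.

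The figures reproduce. They concern differences between groups in a marker measured at one time. They say nothing about change in cognition or new dementia.

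**2. Timeline of direct cognitive tests (Table 1 and the 48 h section).**
- Planned window: 48 − 4 = 44 h to 48 + 4 = 52 h after surgery.
- Outer limit: 60 h, and 60/24 = 2.5 days.
- Scheduled direct cognitive tests of the patient after 60 h: 0.
- MMSE-2 values per patient: at most 1, so MMSE-2 change scores: 0.
- CSF samples per patient: 1, taken after the fracture.

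**3. What the 1-month evidence is.**
- The record review looks for dementia that was documented before the fracture.
- The Participants section describes the IQCODE as a proxy for cognition before the fracture, used for grouping.
- A footnote to Table 1 allows the records, medication data and IQCODE to be obtained at any time until the 1-month window closes, so they are not tied to a fixed follow-up time.
- The Design section uses the records and, where no diagnosis is documented, an IQCODE of 3.31 or above to decide the final group.
- The Sample size section moves a Group 2 patient with evidence of dementia at 1 month into the dementia group.

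So if a new case did surface by 1 month, it would be counted as membership of the dementia group and not as an outcome.

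**4. Aims against data.**

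| Stated aim | What it needs | What is scheduled |
|---|---|---|
| Progression or deterioration | Cognition before, and again after the acute period | Nothing direct after 60 h |
| Exacerbation as lasting worsening | As above | As above |
| Exacerbation as acute worsening | A value from before the fracture on the same scale | MMSE-2: none. AMT/4AT: first score is already after the fracture |
| Developing dementia at follow-up | Dementia-free at baseline, then a later assessment | One classification, aimed at the pre-fracture state |
| Aβ interactions on clinical outcome | A defined outcome | Undefined; the MMSE-2 gives acute status only |
| Elevated markers across three groups | One sample per patient | Available |

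Only the last row is fully served.

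**The case against.** The best defence is that the broad sentences are framing. The sentence before the Abstract's exacerbation claim names the tested hypothesis as elevated biomarkers. The Primary objective, the Primary hypothesis (an acute brain injury) and the sample size all concern marker differences at one time. That stands, and it is why the primary analysis is not in question. It does not cover the Secondary objectives, where new dementia at follow-up and a clinical outcome are set as questions to be answered.

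A second defence is that an article condenses the full protocol and that a separate analysis plan is announced. Which variable serves as the clinical outcome can fairly be left there. But Table 1 is presented as the collection schedule and ends at 1 month. An analysis plan cannot supply an assessment that is not collected.

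Three stronger readings are tempting, and the article does not support them:
- A reader might infer that only the acute state is observed. The 1-month records, the IQCODE and the additional clinical measures are also collected. The accurate statement is that no direct cognitive test is scheduled after 60 h, and that the specified 1-month dementia evidence describes the pre-fracture state.
- A reader might infer that a 48 h MMSE-2 association will be reported as exacerbation. No section says so. The Primary hypothesis section uses cognitive scores only to compare groups.
- A reader might infer that the model of functional scores has no data behind it, because Table 1 lists no functional scale. The text refers to informant-based scores, and the IQCODE is an informant instrument, so this is no ground for deleting the model.

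**Conclusion.** The point holds as a mismatch between stated aims and scheduled data. All 400 planned fracture patients are affected: none has a scheduled direct cognitive test after 60 h, and new dementia cannot be told apart from the classification that forms the groups. The clearest defect is the objective on developing dementia at follow-up. The claims of progression, exacerbation and deterioration in the Abstract and Discussion come next.

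The conclusion assumes that the published schedule is complete as to patient contacts, and that the unspecified 1-month clinical measures include no repeat cognitive assessment. It does not depend on reading exacerbation as lasting, because acute worsening from the pre-fracture state is not measured directly either. The three-group biomarker comparison is sound on this point.

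**What to change.** - **Secondary objectives.** Drop the part on developing dementia at follow-up. Restate the Aβ question as association with dementia status as classified at 1 month, that is, prevalent dementia.
- **Clinical outcome.** Where it rests on the 48–60 h MMSE-2, call it acute post-operative cognitive status, not decline.
- **Abstract and Discussion.** Limit the aims and conclusions to differences in acute inflammation and brain-injury markers, in line with the Primary objective and Primary hypothesis.
- **Primary hypothesis, cognitive and functional scores.** Keep the model and name the informant score. If it is the IQCODE, say that the group comparison is partly circular, because a score of 3.31 or above assigns patients without a documented diagnosis to the dementia group.

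Change in AMT/4AT should not be adopted as an outcome with each patient as their own baseline. The pre-operative score is taken after the fracture, and the Design section says that confusion then may be an acute reaction to it. The same score selects Groups 1 and 2, which brings regression to the mean in Group 1 and a ceiling in Group 2.

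The cost is wording only, with no new visit or test. The downside is a narrower stated claim.

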**Trial registration:**

ISRCTN43803769. Registered 11 May 2017.

## Background

Inflammation is a beneficial physiological response to tissue damage or infection. However, when inflammation is extensive or not fully resolved, this can damage healthy tissues and disrupt normal cellular function. Hip fracture represents a substantial systemic inflammatory trauma, common in older people, which may constitute a significant insult to the degenerating brain and therefore contribute to the progression or even the onset of dementia. Hip fracture in older people has therefore been linked with poor cognitive outcomes, including delirium in the short-term, increased dependency and cognitive decline, especially in patients with dementia [1–3].

The association and pathological role of inflammation in dementia has been extensively described [4]. Studies have shown that microglial cells (the brain’s main macrophage population) are activated in the vicinity of amyloid plaques in dementia [5]. More recent studies suggest that altered macrophage function may contribute to dementia [6]. Animal studies have shown that microglial activation is a consistent feature in dementia and there is evidence that inflammation contributes to the disease process [7, 8] but the physiological and molecular basis for this remains unclear.

Current evidence from human epidemiological studies, human data from blood, cerebrospinal fluid and imaging, and animal models, have established that alongside chronic localised inflammation resulting from and contributing to neurodegenerative diseases such as dementia, there is also neurodegeneration induced by acute inflammatory processes [9] and changes in amyloid processing [10]. Understanding this alternative route to neurodegeneration is becoming increasingly important as the population ages. This is because acute systemic inflammatory episodes, such as infection and inflammatory trauma, are common in older people with some evidence of this having both acute [11] and lasting [12] impacts on cognitive function. Therefore, it is plausible that such episodes are an important cause of decline in people living with dementia, which is clinically almost completely unaddressed.

With rapid advances in identifying and measuring/testing cerebrospinal fluid (CSF) and blood biomarkers of brain inflammation, brain injury and Alzheimer-associated amyloid β (Aβ) plaque pathology, there is the opportunity to study this in humans.

Previous studies in older people with acute systemic inflammation have been limited by small sample sizes, the lack of adequate control groups and, in particular, have not assessed the impact of inflammation on recently emerging biomarkers of new brain injury [13].

One of the other difficulties encountered by research in this area is that hip fracture is an emergency and studies cannot directly collect pre-fracture data. However, well-validated methods for the assessment of pre-fracture cognitive ability are available. The Informant Questionnaire for Cognitive Decline in the Elderly (IQCODE [14] is one example widely-used clinically and for research purposes.

In the United Kingdom (UK) a significant proportion of hip fracture patients undergo surgery within spinal anaesthesia [15]. This routine clinical procedure involves inserting a needle into the patient’s spinal space (subarachnoid space) and injecting anaesthetic into the CSF. In this way, CSF can be collected just before the initiation of anaesthesia, using the same needle that will be used to administer the anaesthetic agent. This means that older patients undergoing emergency hip fracture repair surgery are a suitable group in which to measure systemic inflammation, brain inflammation and CSF markers of brain injury.

The impact of Acute SystematiC inflammation upon cerebRospinal fluId and blood BiomarkErs of brain inflammation and injury in Dementia: a study in acute hip fracture patients (ASCRIBED) will use the opportunity provided by hip fracture operations undertaken via spinal anaesthesia to investigate the impact of acute systematic inflammation upon CSF and blood biomarkers of brain inflammation and neuronal injury and on the exacerbation of dementia. We will collect samples from patients with and without dementia who are suffering a systematic inflammatory response (the ASCRIBED cohort). We will compare ASCRIBED’s ‘unstable’ groups (termed as to refer to the inflammatory response) with an existing cohort of patients living with dementia who have not experienced a systemic inflammatory response from an injury (henceforth known as the ‘Oslo’ cohort). The Oslo cohort will therefore provide ‘stable’ comparators. The study will shed light on the ability of acute inflammatory trauma to produce new brain injury in a vulnerable older population. The findings will then inform the search for new treatments targeting inflammation in dementia.

## Methods

### Aims and objectives

In order to have specific measures informing on the severity of prevalent systemic inflammation at the time of lumbar puncture (i.e., the time of CSF collection), matched to those inflammatory mediators occurring in the CSF, we will quantify inflammatory mediators (including but not limited to IL-1β, TNF-α, IL-6) in both peripheral blood and in CSF. In order to assess brain injury we will measure CSF markers of brain injury (including but not limited to total and phosphorylated tau [T-tau and P-tau, respectively], neurofilament light [NfL] and neurogranin). Brain injury markers will also be measured in blood. Aβ42/40 ratio in CSF and plasma, measured using immunoassays (Meso Scale Discovery and Simoa methods, respectively), will be used as a biomarker of cerebral Aβ pathology. We will also collect an additional 2.5 ml of whole blood from patients. Several studies have recently been published using PAXgene blood collection tubes for later transcriptomic analysis. Our intention is to place ourselves in the position to examine blood signatures that associate with, and may be predictive of, particular CSF and clinical outcomes in our patients for later analysis. Banking these samples will enable further in-depth analysis and is in accordance with the trial ethical approval and consent process.

#### Primary objective

To determine whether hip fracture patients living with dementia show elevated markers of brain inflammation in comparison to (1) stable patients living with dementia and (2) hip fracture patients without dementia, as measured by biomarkers in CSF. CSF inflammation will be measured by TNF-α, IL-1RA, IL-1β, IL-6 and brain injury and biomarkers will be measured by NfL, neurogranin, T-tau, synaptotagmin and SNAP-25.

#### Secondary objectives

To determine whether the magnitude of the brain inflammatory response predicts the quantity of specific brain injury markers measured in the CSF. Magnitude of the brain injury will be assessed via brain injury markers T-tau, P-tau, NfL, neurogranin, synaptotagmin and SNAP-25 in CSF. We will also examine if patients who are Aβ-positive at baseline are more or less likely to have dementia or develop dementia at follow-up. We will also look for interactions of Aβ positivity with the other biomarkers in regards to clinical outcome.

### Design

This observational study will recruit patients with proximal hip fractures who undergo surgery via spinal anaesthesia. The majority of patients admitted with a hip fracture are cognitively vulnerable. This may be a pre-fracture state or an acute reaction to the hip fracture. Clinically, patients arriving in acute settings do not always arrive with a confirmed dementia diagnosis. However, in the UK, it is routine clinical practice to cognitively screen hip fracture patients over the age of 60 years. In England, the Abbreviated Mental Test (AMT) is commonly used [16]. In Scotland, the 4AT is used as best standard practice [17]. Because evidence highlights that the mapping of a patient’s score on the 4AT on to the AMTS is possible [18, 19], we will use routinely available clinical data to pre-operatively assign recruited patients to one of two groups, either ‘confused’ or ‘non-confused’. In this way, we will employ the term confusion to reflect the real-world complexity of the acute hospital environment and initially assign patients accordingly, based on these existing cognitive clinical screening practices (see Fig. 1). Specifically, Group 1 patients will have a pre-op AMT score of ≤8 (England), or a 4AT score of > 1 (Scotland); and Group 2 patients will have a pre-op AMT score of > 9 (England) or 4AT score of 0 (Scotland).

**Fig. 1 Fig1:**
[figure not shown]
Study Diagram and Group Allocation of Patients

Whilst these are indicative of the possibility that the patient may have some form of dementia/cognitive impairment, it is often not possible to obtain confirmative evidence until at least 1-month post-op. Using the AMT or 4AT scores allows us to allocate patients to a group at the recruitment stage. However, we will also take into account any subsequent evidence of dementia in the analysis, by gaining permission/consent to access a patient’s notes and/or where possible, a consented suitable informant (someone who has contact with the patient at least once a month face-to-face or via telephone) via the Informant Questionnaire for Cognitive Decline in the Elderly (IQCODE). This will inform what final group cohort the patient is then allocated to. In the absence of a formal documented diagnosis of dementia and in accordance with previous research [20, 21], patients with an associated suitable informant IQCODE score of 3.31 and above will be assessed as having sufficient evidence of dementia to be allocated to the corresponding group cohort.

### Setting

The study setting is acute trauma wards in hospitals across England and Scotland to which individuals suffering Neck of Femur (NoF) fractures are admitted. In all instances, the investigator(s) will be able to demonstrate a potential for recruiting the required number of suitable participants within the agreed recruitment period (i.e. the investigator(s) regularly treat(s) the target population). For these reasons, the study management team will target NHS Hospitals with large annual admission rates of NOF fractures with sufficiently high percentages of operations being undertaken via spinal anaesthesia. This information was readily available through the National Hip Fracture Database (NHFD) for all NHS Trusts in England [16]. In Scotland, we targeted large centres known to the study group and with existing expertise in collecting CSF for research purposes.

